## Abstract

**Introduction:**

Urgency urinary incontinence (UUI) is characterized by involuntary urine leakage immediately after reporting of sudden, compelling desire to void. Electrostimulation and non-invasive neuromodulation have been considered as the first and third line of UUI treatment but there is a lack of consensus on which parameters are more efficient. Thus, this study aims to compare the effect of low versus medium frequency currents on urinary incontinence severity and quality of life in women with UUI complains.

**Methods:**

It will be a randomized controlled trial with 5 arms, double-blinded (outcome assessor and statistician). The study was approved by the Research Ethics Committee (CAAE: 11479119.9.0000.5406) and has been prospectively registered on the Brazilian Registry of Clinical Trials (RBR-8bkkp6). Concerning, double-blind process, the blinded assessor will be responsible for evaluate primary and secondary outcomes at baseline and follow-up without information about allocation and the statistician will perform analyses without information about group codification. One hundred and five participants will be randomized to receive: (1) Transcutaneous tibial nerve stimulation-low frequency, (2) Transcutaneous tibial nerve stimulation-high frequency, (3) Aussie median frequency, (4) Interferencial median frequency or (5) High voltage stimulation. The application will be performed during 20 sessions of 45-minutes, twice a week for 10 weeks, in groups of maximum 5 participants. The participants will be evaluated before treatment (baseline- 0 week), during the treatment (5 weeks) and after the last treatment session (10 weeks). The primary outcomes measures will be UI severity and quality of life, and the secondary outcome will be pelvic floor strength. Statistical analysis will be performed using SPSS software version 24.0 for Windows (IBM Corp., Armonk, N.Y., USA). The variables will be described by the mean and 95% confidence interval. The distribution of normality will be analyzed by the Shapiro-Wilk test. ANOVA for repeated measures will be performed. Mauchly’s test the hypothesis of sphericity and when if this violated the hypotheses, the analyses will be based on the Greenhouse-Geisser test. Peer-to-peer comparisons will be performed using the Bonferroni Post-Hoc test. The significant level adopted will be 5% (p ≤ 0.05).

**Conclusion:**

This study will enhance knowledge about effect of different neuromodulation currents in the improvement of UUI.

## Background

Urinary incontinence (UI) is a public health problem and affects millions of women worldwide [1]. Defined as involuntary loss of urine [2] UI negatively impact social, economic, familiar, and sexual life aspects [3, 4]. Urgent urinary incontinence (UUI) is characterized by involuntary urine leakage associated with urgency [2] and, in addition to the negative impacts already mentioned, it also causes embarrassment [4]. The prevalence of UUI varies between 5 to 50% of the world population and may increase in elderly population [5].

Although the electrostimulation of pelvic floor muscles (PFM) has been considered as the first line of treatment for UUI [1], neuromodulation delivery by transcutaneous electric nerve stimulation (TENS) via tibial nerve is widely used in clinical settings for being easy to handle, has good acceptance and offering minimal contraindications and collateral effects [5]. TENS can be performed by placing electrodes in the suprapubic, perineal, tibial, or sacral region, however, the application in the region of the tibial nerve is undoubtedly the most used [5]. The heterogeneity on reporting of duration, frequency, work cycle, current, form of administration, and type of electrodes to manage UUI, restrict the knowledge of its effects on bladder modulation due to potential different mechanisms related to doses applied.

The most therapeutic neuromodulation TENS parameters used for urgency symptoms treatment are low pulse width (200 μs) and low frequency (10 Hz) [6], but other therapeutics possibilities have being studied and showed their beneficial effects [7]. Medium frequency currents, such as Aussie and Interferential, are modulated to offer the effect of low frequency current with the benefit of reduced unpleasant effects, such as pain or skin irritation [6].

The Aussie current has been suggested as an option due to its comfort during application, as well as reducing the impedance of the skin ensuring that the pulse of the current reaches deeper tissues [8]. The Interferential current is based on two medium frequency currents that interfere between each other and produce a low frequency resultant current. Its main effects are the significant increase in the pain threshold, which implies more current pleasant sensation [9] with the benefit of reaching deeper tissues [10]. The High Voltage current is also single-phase and pulsed, with double peak and reaches sensory and motor nerve fibers responsible for nociceptive impulses, in addition, when modulated to low frequencies produce a pleasant sensation [11].

Despite the neuromodulation options described in the literature for improving UUI, the evidence is not conclusive, mainly because is still not clear whether the improvement in symptoms occurs due to the application of a specific type of electric current or if the parameters applied are responsible for the improvement. Therefore, the objective of the study will be to compare the effects of applying low frequency currents versus medium frequency currents on severity and quality of life at before treatment (baseline- 0 week), during the treatment (5 weeks) and after the last treatment session (10 weeks) in women with UUI. Our hypothesis is that medium frequency currents may be more effective in UUI treatment when compared to low frequency currents, considering that higher frequencies reduces skin’s impedance which implies delivery of the electrical current to deeper tissues and promotes more assertive stimulation to the tibial nerve which is involved on bladder activity modulation.

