### Sample size and power analysis

A priori sample size calculation was performed using the G* Power 3.1 software. As the innovative comparisons methodology of this trial did not allow us to state our sample calculation on literature data, we calculated our sample size, based on F tests, ANOVA: repeated measures, within-between interactions, an effect size f of 0.17 were calculated considering a direct method using a small partial eta square (*n*^2^) of 0.03. Considering that we selected 5 therapies with potential treatment effects and we expect minimal differences between them, we considered the small effect size calculated by this appropriated method. In addition, we selected a power of 0.85, α error probability of 0.05, number of groups 5, number of measures 3, correlation among repeated measures of 0.5 and nonsphericity correction of 1 and a 10% dropout rate which estimated the recruitment of 105 participants, 21 per group.

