### Outcome measures

#### Primary outcome measure

The primary outcomes will be: 1) UI severity and 2) quality of life.

1) ISI is a validated questionnaire to Portuguese, that classify UI according to severity by multiplying two simple and brief questions about incontinence frequency and volume. The severity score is stratified into mild (one to two points), moderate (three to six points), severe (eight to nine), or very severe (total of 12 points) [19]. The ISI questionnaire will be applied in all time-points.1) Voiding diary is a self-real-life-assessment of voiding habits [22]. The 24-hour voiding diary shows greater acceptance by patients, but three-day voiding diary seems to be more suitable for possible evaluative interpretations [3]. The participants will fulfill during entire 3-days (72h) detailed information (including time of the event) about fluid intake (quantity), voiding (volume for each), leakage (time and associated reasons) and pad changes [22]. The voiding diary will be applied in all time-points.2) The ICIQ-SF is a brief self-administered questionnaire combined severity and bother-score through 4 questions about incontinence frequency, volume, impact of UI in daily life and self-diagnosis questions about mechanism reasons. The higher the score obtained is, the worse the quality of life related to that domain is [16]. The ICIQ-SF questionnaire will be applied in all time-points.2) The OAB-V8 will be used to assess the impact of overactivity bladder symptoms on quality of life. It is a questionnaire composed of 8 questions about the discomfort caused by the symptoms. The responses range from 0 to 5 points and in the sum of the results, if the total is ≥ 8, it will be considered as a probable diagnosis for UUI [17]. The OAB-V8 questionnaire will be applied in all time-points.2) The ICIQ-OAB questionnaire provides an assessment measure for voiding frequency, urgency, nocturia, and UI. It is composed of six specific questions about voiding symptoms correlating with quality of life, and the higher the score the worst the impairment [18]. The ICIQ-OAB questionnaire will be applied in all time-points.

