### Statistical analysis

The study will be run as a superiority trial. The statistical analysis will follow the per-treatment concept. Statistical analysis will be performed using SPSS software version 24.0 for Windows (IBM Corp., Armonk, N.Y., USA). The variables will be described by the mean and 95% confidence interval (95% CI). The distribution of normality will be analysed by the Shapiro-Wilk test. To analyse the effect of group and currents, ANOVA for repeated measures will be performed. The Mauchly’s test will be performed to test the hypothesis of sphericity and when if this violated the hypotheses, the analyses will be based on the Greenhouse-Geisser test. Peer-to-peer comparisons will be performed using the Bonferroni Post-Hoc test. The significant level adopted will be 5% (p ≤ 0.05).

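### No primary time point is named: week 5 (mid-course) and week 10 (after the last session) have equal standing, so nothing prevents a week-5-only difference from being reported as superiority.

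*Protocol article*

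**What the plan says.** All references are to the protocol article.

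- **Background (objective):** the currents are compared, for both outcome domains, "at before treatment (baseline- 0 week), during the treatment (5 weeks) and after the last treatment session (10 weeks". The three times stand in one list, and none is marked as decisive.
- **Primary outcome measure:** "The primary outcomes will be: 1) UI severity and 2) quality of life". No time is attached to either. For the severity index, "The ISI questionnaire will be applied in all time-points", and the same is said of the voiding diary, ICIQ-SF, OAB-V8 and ICIQ-OAB.
- **Sample size and power analysis:** the calculation is "based on F tests, ANOVA: repeated measures, within-between interactions", with five groups and three measures.
- **Statistical analysis:** "The study will be run as a superiority trial". "To analyse the effect of group and currents, ANOVA for repeated measures will be performed". "Peer-to-peer comparisons will be performed using the Bonferroni Post-Hoc test". No effect, contrast or visit is named as the one that decides, and no rule for declaring superiority is given.

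By contrast, the secondary outcome (pelvic floor strength) is measured only at baseline and week 10, so its endpoint time is clear.

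**The concern.** Treatment is 20 sessions over 10 weeks, so week 5 falls at the halfway point. A difference between currents at week 5 concerns speed of response; a difference at week 10 concerns the result of the full course. The hypothesis and the conclusion are about which current or parameters work better for urgency incontinence, which is most naturally the second question.

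The interaction test only asks whether the five profiles over weeks 0, 5 and 10 are parallel. It does not show where they separate. The pairwise comparisons could show this, but they are not assigned to a visit. A mid-course difference that has gone by the end of treatment could thus be reported as superiority, and the team could settle on a week once results are known. The gap exists even for one instrument and one pair of arms, so it is separate from the number of primary instruments and from the choice of contrast between low- and medium-frequency arms.

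**Working it through.** **1. The plan's own sample size.** Inputs from the sample size section: partial eta squared 0.03, alpha 0.05, power 0.85, k = 5 groups, m = 3 measures, correlation 0.5, nonsphericity correction 1, 10% dropout.

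- f² = 0.03/0.97 = 0.03093, so f = 0.1759 (the article gives 0.17).
- Interaction test: λ = f²·N·m/(1 − ρ), df = (k − 1)(m − 1) = 8 and (N − k)(m − 1).
- At N = 95: λ = 0.03093 × 95 × 3/0.5 = 17.63, df 8 and 180, power 0.853.
- 95 × 1.1 = 104.5, rounded up to 105. The stated 105 (21 per arm) is reproduced, which confirms that the interaction is the effect the trial is powered on. It leaves 95/5 = 19 evaluable per arm.

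**2. Is that test sensitive to timing?** Keep the same f and place the between-arm effect in four assumed time patterns over weeks 0, 5 and 10 (the article gives none). The SD of the arm means at full effect is s = √(f²/v), where v is the variance of the pattern over the three visits. For a test at week 10 adjusted for baseline, the residual variance is 1 − 0.5² = 0.75, and λ₁₀ = 95·s₁₀²/0.75 with df 4 and 89, where s₁₀ is the SD of the arm means at week 10.

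| Pattern (0, 5, 10) | v | s | Interaction power | λ₁₀ | Week-10 five-arm power |
|---|---|---|---|---|---|
| builds (0, ½, 1) | 1/6 | 0.431 | 0.853 | 23.5 | 0.98 |
| sustained (0, 1, 1) | 2/9 | 0.373 | 0.853 | 17.6 | 0.92 |
| week 10 only (0, 0, 1) | 2/9 | 0.373 | 0.853 | 17.6 | 0.92 |
| week 5 only (0, 1, 0) | 2/9 | 0.373 | 0.853 | 0 | 0.05 |

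The interaction has the same power in all four rows, including the one with no difference at the end of treatment.

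**3. One arm better at week 5 only** (assumed: 19 per arm, normal outcome, SD 1, correlation 0.5, difference d). The squared interaction effects sum to d² × (1 − 1/5) × (1 − 1/3) = 0.533 d², and λ = 19 × 0.533 d²/0.5.

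- d = 0.6: λ = 7.3, power 0.42
- d = 0.8: λ = 13.0, power 0.70
- d = 1.0: λ = 20.3, power 0.91

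Simulation agrees (0.41 to 0.42, 0.70 to 0.71, 0.90). At every d, the chance of any Bonferroni-significant pair at week 10 is about 4%. At d = 0.8, about 50% of trials show a significant interaction with a significant pair at week 5 and none at week 10.

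**4. False positives with no true effect** (same assumptions, ten pairs per visit, Bonferroni over the ten). At least one significant pair:

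- at week 10 alone: about 4%
- at week 5 or week 10, without first requiring a significant interaction: about 7%
- at week 5 or week 10, only after a significant interaction: about 1%

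**5. Power of one pair at week 10.** Noncentrality = d/√(2/19); critical t at two-sided 0.05/10 = 0.005 with 90 df is 2.88. At d = 0.8 the noncentrality is 2.47 and power is 0.35, without baseline adjustment. At 0.6 and 1.0 SD it is 0.16 and 0.58.

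**The case against.** The best defence is that this is a condensed article and the analysis plan is not shown. A repeated-measures ANOVA sized on the interaction is a coherent comparison of response profiles, and the visit used for post-hoc pairs is often left to the analysis plan. The text also leans towards the end of treatment: week 5 is described as falling during treatment, and the secondary outcome is measured only before and after the course.

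Part of this stands. The interaction is a legitimate test and keeps its 5% level. But the deciding time is part of the definition of a primary outcome and not an analysis detail, and the article states the objective at several times without ranking them. The lean towards week 10 is not a rule.

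The week-5-only pattern is also an assumption. Treatment continues unchanged to week 10, and under the other three patterns the interaction and a week-10 test would usually agree. The figures show what the plan fails to exclude, not what is likely.

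Four stronger readings are tempting, and the document does not support them:

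- **That the plan prescribes superiority from week 5.** It states no success rule; it only leaves this open.
- **That baseline competes as a deciding time.** The objective lists it, but in this analysis it is the reference for change. The real ambiguity is week 5 versus week 10.
- **That the type I error is inflated.** This holds only if pairs are tested at both weeks without gating on the interaction. The article does not say which procedure applies.
- **That conflicting pairwise verdicts at the two weeks show the harm.** With an equal true effect at both weeks, verdicts on one pair differ in roughly 30% of trials, but this mostly reflects low pairwise power, which naming a week does not cure.

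**Conclusion.** The point holds in a limited form. No primary time point is named, and neither the test that sizes the trial nor the pairwise comparisons are tied to a visit. A week-5-only difference could therefore be reported as superiority, or the week picked after the data are seen, without departing from the plan.

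The main fault is an undefined question; error inflation is secondary and conditional on ungated testing. The sizes in the working rest on 19 completers per arm, normal outcomes, correlation 0.5 and time patterns that the article does not supply. The change should be made, because it settles what the trial's conclusion means at little cost.

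**What to change.** In the objective (Background) and in Statistical analysis, state that:

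- the primary comparison on each primary outcome is the between-arm difference at week 10, adjusted for the baseline value;
- a five-arm test at week 10 comes first, and the Bonferroni pairwise comparisons, also at week 10, follow it;
- week-5 comparisons are secondary and describe speed of response;
- baseline serves only as covariate or reference.

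Data collection is unchanged, and the text needs only a few sentences.

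There are two costs. A current that only acts faster could be claimed superior only on a secondary comparison. Power must also be restated for the week-10 test. On the article's own effect size, the baseline-adjusted five-arm test has about 0.92 to 0.98 if the effect persists or builds, so 105 need not rise for that test. A single Bonferroni pair without baseline adjustment has only about 0.35 at 0.8 SD, so pairwise power should be checked and reported separately.

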## Material and methods

### Design

A five-arm, parallel randomized controlled trial, double-blinded (outcome assessor and statistician), will be performed. All personal data will be confidential. The study follows the TIDieR (Template for Intervention Description and Replication) checklist [12], the 2013 Standard Protocol Items: Recommendations for International Trials statement [13] (Fig 1), and the Consort guidelines [14] (Fig 2).

**Fig 1 pone.0276722.g001:**
[figure not shown]
Schedule of the study protocol according to the standard protocol items: Recommendations for interventional trials checklist.

**Fig 2 pone.0276722.g002:**
[figure not shown]
Consort flowchart.

### Ethical approval and consent

The study was approved by the Research Ethics Committee (CAAE: 11479119.9.0000.5406). All participants will be informed about the research and will sign a consent form. The protocol of this study has been prospectively registered on the Brazilian Registry of Clinical Trials (RBR-8bkkp6). Participants will be informed about all study procedures and asked to sign the Informed Consent Form prior to their enrollment in the study.

### Participants

#### Recruitment

Women with UUI will be recruited from a waiting list from the Specialized Center for Women’s Health Rehabilitation of the São Paulo State University, Marília, São Paulo, Brazil.

### Eligibility criteria

#### Inclusion and exclusion criteria

Potential participants will be eligible for the study if they are between 18 to 80 years old with complaints of UUI. Potential participants will be ineligible for the study if they have cognitive impairment, psychiatric disorders, pregnancy, diagnosis of neurogenic bladder, pelvic organ prolapse greater than grade II, ongoing signs and symptoms of urinary tract infections, use of anticholinergic drugs, antagonists calcium, beta-antagonists, and dopamine antagonists, cannot commit to participating for the duration of treatment and those who do not sign the consent form.

### Clinical assessment

#### Physiotherapeutic evaluation

Potential participants who fulfil the eligibility criteria undergo baseline assessments. The protocol will include anamnesis and physical assessment, the clinical screening will be carried out at São Paulo State University and will take approximately 30 minutes.

A registered physiotherapist with 8 years of experience on urogynecological examination, and who has a Master in Gynecology and Obstetrics field supervised by physiotherapist that has more than 30 years of urogynecological assessment experience will perform the evaluation. Both assessors will not be enrolled on the screening, randomization and/or treatment routine to ensure blinding assessment regardless the treatment type.

The first step of data collection will be related to anthropometric data (age, weight, height, and BMI), personal information, demographic partner (profession, race and education) and pathological and clinical history. The personal data of the participants will be numerically coded and stored in a database.

The second step of data collected will be the physical examination. PFM function will be assessed through the PERFECT scheme [15] and will be held in a reserved and adequate room. In addition, they will answer four different questionnaires regarding UUI. The International Consultation on Incontinence Questionnaire- short form (ICIQ-SF) [16], the Overactive Bladder Questionnaire (OAB-V8) [17], the International Consultation on Incontinence Questionnaire Overactive Bladder (ICIQ-OAB) [18] and the Incontinence Severity Index (ISI) [19]. At the end of the baseline assessment and before the first treatment session, participants will receive the voiding diary and instructions to complete it at home during 3 different days. All questionnaires, including the voiding diary, will be administered in Portuguese (Brazil) according to their respective validated versions.

The same blinded assessor will evaluate the participants before treatment (baseline- 0 week), during the treatment (5 weeks) and after the last treatment session (10 weeks).

### Sample size and power analysis

A priori sample size calculation was performed using the G* Power 3.1 software. As the innovative comparisons methodology of this trial did not allow us to state our sample calculation on literature data, we calculated our sample size, based on F tests, ANOVA: repeated measures, within-between interactions, an effect size f of 0.17 were calculated considering a direct method using a small partial eta square (*n*^2^) of 0.03. Considering that we selected 5 therapies with potential treatment effects and we expect minimal differences between them, we considered the small effect size calculated by this appropriated method. In addition, we selected a power of 0.85, α error probability of 0.05, number of groups 5, number of measures 3, correlation among repeated measures of 0.5 and nonsphericity correction of 1 and a 10% dropout rate which estimated the recruitment of 105 participants, 21 per group.

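### The sample size text gives 85% power for a partial eta squared of 0.03, but 105 women give about 32% to 37% for that effect in its usual sense; the calculation actually powers about 0.085 to 0.09

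*Protocol article*

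**What the plan says.** Under Sample size and power analysis, the Protocol article says the calculation was "based on F tests, ANOVA: repeated measures, within-between interactions". The effect size is given as "an effect size f of 0.17 were calculated considering a direct method using a small partial eta square", with the value 0.03. The other inputs are "we selected a power of 0.85", "α error probability of 0.05", five groups, three measures, a correlation of 0.5 among repeated measures, a nonsphericity correction of 1 and 10% dropout. The result is 105 women, 21 per arm. The choice of effect is justified by the five therapies all being potentially active: "we expect minimal differences between them, we considered the small effect size calculated by this appropriated method".

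Under Statistical analysis, the trial is described as a superiority trial, analysed by repeated-measures ANOVA with Bonferroni-adjusted pairwise comparisons. The software is named: "Statistical analysis will be performed using SPSS software version 24.0 for Windows".

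**The concern.** A partial eta squared for a group-by-time interaction is the interaction sum of squares divided by itself plus the within-subject error sum of squares. Stable differences between women have already been removed from that error, so the gain from within-person correlation is already inside the ratio. If the ratio is turned into f, and f then goes into a formula that divides by (1 − correlation), the gain is credited a second time.

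What is at stake is how the result will be read. The article ties its sample size to a small effect among five active treatments. If the trial is powered only for a much larger interaction, a non-significant test is the likely outcome at the stated effect and says little about whether the currents differ. Someone relying on the 85% would give that result more weight than it can bear.

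**Working it through.** **Inputs, all from the sample size section.** Groups k = 5, measures m = 3, correlation ρ = 0.5, nonsphericity correction 1, α = 0.05, target power 0.85, dropout 10%, partial eta squared 0.03.

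**Test.** Interaction F test with df1 = (5 − 1)(3 − 1) = 8 and df2 = 2(N − 5). Power comes from the noncentral F distribution with noncentrality λ. At N = 95, df2 = 180 and the 5% critical value is 1.99.

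**Step 1: reproduce the plan's figure.**
- f² = 0.03/0.97 = 0.03093, so f = 0.1759 (printed as 0.17).
- λ = f² × N × m/(1 − ρ) = f² × N × 6.
- At N = 95: λ = 0.03093 × 95 × 6 = 17.63, power 85.3%. This is the smallest N that reaches 85%.
- Dropout: 95 × 1.1 = 104.5, hence 105.

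The stated total therefore reproduces. Of the routes checked, this is the only one that gives it.

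**Step 2: take 0.03 in its ANOVA sense.** The correlation is already in the ratio, so λ = f² × 2(N − 5). A common variant is f² × 2N. Both are shown.

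| Women analysed | λ | Power at partial eta squared 0.03 |
|---|---|---|
| 95 | 5.57 to 5.88 | 31.7% to 33.5% |
| 105 | 6.19 to 6.49 | 35.4% to 37.2% |

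Simulation (20,000 trials per setting, effect set on the 2N convention) gave 33.6% at 95 and 37.4% at 105. Simulating the Step 1 effect at 95 gave 85.4%.

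The multiplier of 6 stands where about 2 belongs: 17.63/5.57 = 3.2 and 17.63/5.88 = 3.0, an overstatement of about threefold.

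**Step 3: find the effect that the calculation does power.**
- Converting λ = 17.63 at 95 completers back to a partial eta squared: 17.63/(17.63 + 180) = 0.089, or 17.63/(17.63 + 190) = 0.085.
- Solving for exactly 85% power gives 0.084 to 0.089 with 95 analysed and 0.077 to 0.080 with 105 analysed.
- For 85% power at 0.03, about 276 to 280 completers would be needed.

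**Step 4: the same effect in SD units.** This needs assumptions that the article does not make: five arm means evenly spaced, 19 women per arm, and a stated time course. Let d be the gap between the best and worst arm in 10-week change, in single-measurement SDs. With ρ = 0.5 this equals the SD of change, since √(2 × (1 − 0.5)) = 1. Then λ = 19 × S × d²/(1 − 0.5), where S is the sum of squared interaction terms for d = 1. For 85% power at 95 completers, λ = 17.50.
- Change linear over weeks 0, 5 and 10: S = 0.3125, d = √(17.50 × 0.5/(19 × 0.3125)) = 1.21.
- Change complete by week 5, or appearing only at week 10: S = 0.4167, d = √(17.50 × 0.5/(19 × 0.4167)) = 1.05.

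**The case against.** The strongest reply is that the arithmetic is sound. The article gives f, a correlation to go with it and the remaining settings, and together they return 105. If f is read as the spread of the interaction effects relative to the SD of a single measurement, dividing by (1 − ρ) is correct and 105 women are enough. This stands. A reader might infer that 105 is a miscalculation or that the trial must be enlarged to about 280 completers, and the document does not support that. The reply does not rescue the paragraph, however. On that reading the powered effect is a partial eta squared of about 0.085 to 0.09, so 0.03 and the small-effect description are wrong.

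A second reply is that the article says the investigators expect minimal differences, not that the trial can detect them, and that it claims superiority and nowhere equivalence. This also stands: a conclusion that the currents are alike is a foreseeable misreading, not a claim in the text. Even so, the expectation is offered as the reason for the effect size behind the sample size, so it presents the trial as sized for such differences.

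Third, the roughly 32% belongs to the 95 women left after the planned dropout, not to all 105. This is correct, and both figures are given. The conclusion is the same for either.

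**Conclusion.** The paragraph is wrong as written on either reading, and the document does not say which was meant. If 0.03 is an ordinary ANOVA partial eta squared, power is about 32% to 33% with 95 completers (35% to 37% with 105), not 85%. If f is relative to the single-measurement SD, 85% holds but for an effect of about 0.085 to 0.09, roughly three times the one named. With evenly spread arms, that corresponds to a best-to-worst gap of about 1.05 to 1.2 SD in 10-week change, depending on the time course.

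These figures rest on the plan's own inputs: five equal arms, three measures, correlation 0.5, sphericity and 10% dropout. Two stronger inferences should not be drawn: that 105 women cannot give 85% power on any reading, and that the investigators claim to be able to show the currents equal.

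**What to change.** In Sample size and power analysis:

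1. Replace the power statement with, for example: *105 women (about 95 completers) give 85% power for a group-by-time partial eta squared of about 0.09, and about 32% for 0.03.* Say how f was defined and where the correlation of 0.5 enters.
2. Remove the small-effect and minimal-differences reasoning as the justification for the sample size.
3. State that a non-significant interaction is inconclusive and is not evidence that the currents are alike.
4. If an effect in SD units is added, give its assumptions on arm spacing and time course with it.

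The cost is wording only. Enrolment and the planned analysis stay as they are, though the stated power becomes less favourable.
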